***Secondary outcomes: *****respiratory muscle strength, vital capacity and walk function**

Patients will be assessed for their respiratory muscle strength (maximal inspiratory pressure (PImax), maximal expiratory pressure (PEmax)) and vital capacity (VC). PImax and PEmax will be assessed with an analog manovacuometer (MTR) with an operating range of 300 cmH_2_O (calibrated before each use) and with the patient in the seated position with relaxed arms and a disposable mouthpiece and nasal opening for the air leak.

To measure the inspiratory muscle strength (PImax), the patient will be asked to perform a maximal expiration to the level of residual volume (RV) and then perform a maximal inspiratory effort, which must be maintained for approximately one second. To measure expiratory muscle strength (PEmax), the patient will be asked to perform a maximal inspiration at the level of total lung capacity (TLC) and then perform a maximal expiratory effort, which must be maintained for approximately one second [19,22,23]. The patient will be encouraged by the evaluator during these procedures to exert his/her maximal effort. The greatest of three consecutive measurements will be used. The mouthpieces used to record respiratory muscle strength have a small opening (± 2 mm) to exclude the force of the facial muscles and make the measurements more reliable.

The vital capacity (VC) will be measured with a spirometer (Wright Mark 8) with the patient in a seated position and connected to a disposable mouthpiece and nose clip to prevent air leakage. The test starts with inspiration to TLC, followed by expiration to the RV. The greatest of three consecutive measurements will be considered [19,22,23].

Assessment of walking function will be performed using the Iowa Gait Test. Patients will be assessed on three items: walking speed, distance travelled and level of assistance while walking for 15 seconds [24]. The evaluator will walk alongside the patient and measure time using a digital timer (Oregon SL 110). The evaluator will not talk during the test to allow the patient to determine his/her own pace and will provide the necessary assistance to the patient when needed. The starting point will be marked with tape, and the patient will be instructed to walk forward as fast and safely as possible and stop when requested. The place where the patient stops will also be marked with tape, and the distance between the two points marked will be measured. Those who cannot walk independently will receive assistance. The levels of assistance will be classified as follows:

• Independent, no assistance

• Minimal assistance, one point of contact (e.g., holding an arm)

• Moderate assistance, two points of contact (e.g., holding both arms)

• Maximum assistance, three or more points of contact (e.g., holding an arm and both hands at the waist)

The saturation of peripheral oxygen (SpO_2_) will be monitored through a pulse oximeter (Nonin Onyx 9500) to ensure proper oxygen saturation during the test. If the SpO_2_ drops below 92% or 10% of the baseline, the test will be stopped.

### Procedure

#### Active TENS group

Patients in this group will receive prescription pain medication for pain control. In addition to primary care, patients will undergo TENS on the first day of the postoperative period, with an exposure time of 1 hr. Pain intensity, pulmonary tests and walking function will be evaluated before and after the intervention with TENS, immediately before the TENS is discontinued.

#### Placebo TENS group

Patients in this group will also receive prescription of analgesics for pain control. Patients will undergo the same procedures as the TENS active group, but the unit will emit electrical current only during the first 30 seconds of the application. One hour after the commencement of the intervention, patients will be subjected to the same tests as described above.

#### Blinding

Two assessors will be involved in the study and will be trained to perform the procedures in this study. Assessor 1 will be responsible for the evaluation of pulmonary tests, walking ability and assessment of pain intensity in all patients in the study. Assessor 2 will be responsible for administering TENS in all patients in the study. Only Assessor 2 will know if the patient received the active or placebo TENS. Both Assessor 1 and the patients will be blinded to the mode of application of TENS. Assessor 2 will instruct patients not to report their perceptions during the TENS administration to the assessor conducting the assessments.

#### Data analysis

The sample size was calculated considering a difference of two points in the verbal numeric pain scale between the TENS active and placebo groups and an estimated standard deviation of 3 based on data from a previous study [25]. For a significance level of 0.05 and 80% power, it was estimated that 37 participants would be required in each group (Minitab, v.15, State College, PA).

The statistical analysis will be performed on an intent-to-treat basis. The effects of the intervention on pain intensity, pulmonary function, and walking capacity, will be calculated using independent samples t tests for normally distributed data. Data not normally distributed will be compared using Mann–Whitney U tests. The level of significance will be set at *α* = .05. The data will be analysed using SPSS software (v.17; SPSS Inc; Chicago, IL) by an investigator who is blind to group allocation.

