**Methods/design:**

Seventy-four patients will be randomly allocated into 2 groups: active TENS or placebo TENS. All patients will be assessed for pain intensity, walk function (Iowa Gait Test), respiratory muscle strength (maximal inspiratory pressure and maximal expiratory pressure) and vital capacity before and after the TENS application. The data will be collected by an assessor who is blinded to the group allocation.

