## Methods and design

### Study design

This study is a prospective randomized controlled and double-blind. Seventy-four patients will be randomly distributed into two groups: active TENS + analgesics (n = 37) and placebo TENS + analgesics (n = 37). Randomization will be performed by an investigator not involved in data collection using the sequentially numbered, opaque sealed envelopes (SNOSE) allocation concealment method [16,17]. Patients will be admitted one day before surgery and will undergo group randomization on the first day of the postoperative period. After randomization, the patients will be assessed for pain intensity, respiratory muscle strength, vital capacity and walking function before and after the use of TENS. The present study was approved by the Research Ethics Committees of University of the City of Sao Paulo and Federal University of Sao Paulo. All participants will receive written and verbal information on the aims and procedures of the study and will sign a consent form to agree to participate in the study.

All patients will be advised on the assessments that will be performed, including general information on the surgical procedure (type and size of the incision, sedation, intubation and need for admission to the Intensive Care Unit). The study flow diagram is presented in Figure 1.

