#### Outcome measures

***Primary outcome: *****pain intensity**

To evaluate pain intensity, an 11-point numeric rating scale (NRS) will be used, where 0 represents no pain and 10 represents the most intense pain imaginable. The assessment will be conducted at rest, during coughing and during respiratory tests (maximal inspiratory and expiratory pressures and vital capacity) and walking function (Iowa Gait Test) before and after administration of TENS [21].

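### The outcomes are measured before and after TENS, but the named tests are unadjusted and do not say which value is tested; baseline-adjusted ANCOVA would add precision at almost no cost

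*Protocol article*

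**What the plan says.** The Study design section states that "the patients will be assessed for pain intensity, respiratory muscle strength, vital capacity and walking function before and after the use of TENS". The Primary outcome section says the same of the pain rating, taken at rest, on coughing, during the respiratory tests and with walking, "before and after administration of TENS". The abstract agrees ("before and after the TENS application"). A pre-treatment value of each measure is therefore planned for every patient, about an hour before the post-treatment value.

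The Data analysis section gives one method for pain, pulmonary function and walking capacity: effects "will be calculated using independent samples t tests for normally distributed data". The fallback is also unadjusted: "Data not normally distributed will be compared using Mann–Whitney U tests". The section mentions no covariate, change score or repeated-measures model.

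The sample size was set "considering a difference of two points in the verbal numeric pain scale between the TENS active and placebo groups", with "an estimated standard deviation of 3 based on data from a previous study", a significance level of 0.05 and 80% power, giving 37 per group. No pre-post correlation enters that calculation.

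**The concern.** An independent samples t test compares one number per patient, and the article does not say which number. There are two candidates.

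- **Post-TENS score.** The pre-TENS value plays no part. Any chance difference between the groups at baseline carries into the estimated effect in proportion to the pre-post correlation.
- **Change score.** The baseline is used, but with a fixed weight of 1. Unless the regression slope of post on pre happens to be 1, this weight is not the best one, and some imbalance remains in the estimate.

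The two can give different answers on the same data when the baselines differ. ANCOVA estimates the weight from the data and, apart from the one degree of freedom it spends, is at least as precise as either. With 37 per group and a design power only just above 80%, this is precision that the planned measurements already pay for.

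**Working it through.** **Inputs.** From Data analysis: difference 2, SD 3, α 0.05, 37 per group. Two-sided testing is assumed; it reproduces the stated number, whereas a one-sided calculation gives 28. From Inclusion criteria: rest pain between 2 and 7 at entry. Assumed: pre-post correlation r of 0.3, 0.5 and 0.7, since the article gives none, and SD 3 read as the SD of a single post-TENS score.

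**Step 1: the plan's own figure.** The exact two-sample t calculation with effect size 2/3 needs 36.3 per group, rounded up to 37. Power at 37 is 80.8%. The stated number is right for the stated test. The standard error of the difference is 3 × √(2/37) = 0.697, and the 95% CI half-width is 1.993 × 0.697 = 1.39 points.

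**Step 2: ANCOVA.** Residual SD = 3 × √(1 − r²). The last column is the unadjusted group size with the same precision, 37/(1 − r²).

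| r | Residual SD | Power at 37 | CI half-width | Equivalent n per group |
|---|---|---|---|---|
| 0.3 | 2.86 | 84.3% | 1.33 | 40.7 |
| 0.5 | 2.60 | 90.4% | 1.20 | 49.3 |
| 0.7 | 2.14 | 97.7% | 0.99 | 72.5 |

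Deducting the degree of freedom for the covariate leaves these powers unchanged to the decimal shown.

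**Step 3: chance imbalance under a post-score test.** If the baseline means differ by 1.96 standard errors, the expected shift in the unadjusted post-score difference is 1.96 × r × 3 × √(2/37) = 1.367 × r. That is 0.41, 0.68 and 0.96 points for r of 0.3, 0.5 and 0.7, against a target difference of 2. The baseline SD cancels, so this does not depend on how narrow the baseline is.

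**Step 4: t test on change scores, rest pain.** SD of change = √(9 + s² − 2 × r × 3 × s), where s is the baseline SD. Values confined to 2 to 7 cannot have an SD above (7 − 2)/2 = 2.5; if spread evenly over the integers 2 to 7, the SD is about 1.7.

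| r | Change, s = 1.7 | Change, s = 2.5 | ANCOVA |
|---|---|---|---|
| 0.3 | about 81% | 73.5% | 84.3% |
| 0.5 | about 90% | 86.2% | 90.4% |
| 0.7 | about 97% | 97.3% | 97.7% |

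ANCOVA is highest in every row, but with the narrower baseline SD the margin is 3 percentage points or less.

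**The case against.** Three stronger readings are tempting, and the article supports none of them.

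**That the analysis ignores the baseline.** A reader might infer this because no covariate is named. But the text speaks of effects of the intervention on measures taken before and after TENS, and a t test on change scores fits that wording. What is established is that the test is unadjusted and the tested value is not identified.

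**That power could fall to 67%.** Change scores with equal SDs of 3 at both times give 66.7% at r = 0.3. For rest pain this cannot apply, because the entry limit caps the baseline SD at about 2.5. Pain on coughing or walking is not limited in this way, but the article gives no SD specific to those conditions.

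**That the loss is large for vital capacity and respiratory pressures.** No SD or correlation is given for them. If r is high, as is plausible for maximal efforts repeated an hour apart, a change-score test would already recover most of what ANCOVA offers. The loss would be large only if post scores were tested.

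It is also fair to say that the planned test is valid: randomisation makes it unbiased on average, it controls the type I error, and the sample size matches it. The entry limit may lower r for rest pain, which makes the modest end of the range plausible there.

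Finally, the choice of covariates, and of post or change score, is often left to an analysis plan. That argument would carry if the article were silent. It is not: it names an unadjusted test for every outcome, so the stated choice is open to comment. These objections limit the size and grading of the point; its direction stands.

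**Conclusion.** The point holds as a recommendation on efficiency. The named method is valid and adequately powered on the plan's own assumptions, but is generally less precise than a baseline-adjusted analysis of the same data, whether post scores or change scores were meant.

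Against a post-score test, ANCOVA raises power from 80.8% to between 84% and 98% for r from 0.3 to 0.7, and removes an expected shift of about 0.4 to 1.0 points when the baselines differ by 1.96 standard errors. Against a change-score test of rest pain, the gain ranges from under 1 to about 11 percentage points over the same r and baseline SDs of 1.7 to 2.5, and may well be small. All these figures rest on an assumed r and on SD 3 being the SD of a single post-TENS score. For the secondary outcomes only the direction can be stated.

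**What to change.** In Data analysis, for pain and each continuous secondary outcome, make the primary analysis a linear model (ANCOVA) with the post-TENS value as response, treatment group as factor and the pre-TENS value of the same measure as covariate. Report the adjusted mean difference with its 95% CI. Keep the unadjusted comparison as a sensitivity analysis, and state whether it uses the post-TENS value or the change.

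The cost is a short change of wording, made before unblinding, and one degree of freedom per model. The baseline values are already to be collected, the named software fits the model, and the 74 patients need not change.

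### The observed shape of the data decides whether the primary pain outcome gets a t test or Mann-Whitney, although the trial is sized on a 2-point mean difference

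*Protocol article*

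**What the plan says.** All references are to the protocol article.

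- **Primary outcome.** For pain, "an 11-point numeric rating scale (NRS) will be used, where 0 represents no pain and 10 represents the most intense pain imaginable". It is rated at rest, on coughing, during the respiratory tests and during walking, before and after TENS.
- **Sample size (Data analysis).** The basis is "a difference of two points in the verbal numeric pain scale between the TENS active and placebo groups", with "an estimated standard deviation of 3 based on data from a previous study". "For a significance level of 0.05 and 80% power", "it was estimated that 37 participants would be required in each group".
- **Analysis (Data analysis).** Effects on pain, pulmonary function and walking "will be calculated using independent samples t tests for normally distributed data". For the rest, "Data not normally distributed will be compared using" Mann-Whitney U tests. The section names no normality check or threshold, and does not say which of the two tests is primary for pain.
- **Inclusion criteria.** Rest pain at entry must lie between 2 and 7.

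**The concern.** The sample size fixes the question: how many points apart are the mean pain scores? The analysis rule leaves the question open until the data are seen. Mann-Whitney tests whether P(X<Y) + 0.5 P(X=Y) equals 0.5. That is a legitimate hypothesis, but it is not about a difference in mean points, and its result cannot be set directly against the 2-point target.

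The outcome makes the second branch a real prospect. Scores are whole numbers with a floor at 0, in patients who enter with rest pain of 2 to 7 and then receive analgesics with active or placebo TENS. The lower scores fall, the more they pile up at the floor and the more readily a normality check fails. The choice of test is therefore partly driven by the result. Because pain is rated under several conditions, the rule can also send rest pain to one test and pain on walking to the other, so the conditions would not share an effect measure.

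**Working it through.** **1. The plan's own figure.** Inputs from Data analysis: difference 2, SD 3, alpha 0.05 (taken as two-sided), power 80%.

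- Normal approximation: n = 2 × (1.960 + 0.842)² × 3² / 2² = 35.3, so 36 per arm.
- Noncentral t: n = 36.3, so 37 per arm, with 80.8% power at 37.

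The stated 37 reproduces as a t-test calculation for a difference in means. A one-sided alpha gives 28 by the normal approximation and does not match.

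**2. How often would the rule switch?** The article gives neither post-treatment means nor a normality check, so the following are assumptions: 37 per arm; scores drawn from a normal distribution, rounded and clipped to 0-10; Shapiro-Wilk at 5%, with a switch if either arm fails. There are 4,000 simulated trials per row. Columns 3 to 5 give the percentage of trials with p < 0.05.

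| Underlying means, SD | Switch | Always t | Always Mann-Whitney | Rule as written |
|---|---|---|---|---|
| 4 v 2, SD 3 | 99.8% | 78.9% | 78.0% | 78.0% |
| 4 v 2, SD 2.2 | 98.5% | 96.4% | 96.1% | 96.1% |
| 5 v 3, SD 3 | 90.3% | 79.6% | 77.9% | 78.3% |
| 5 v 3, SD 2.2 | 68.3% | 96.6% | 96.1% | 96.3% |
| 6 v 4, SD 3 | 69.0% | 79.4% | 77.7% | 78.2% |
| 6 v 4, SD 2.2 | 39.1% | 96.4% | 96.0% | 96.4% |
| no effect, 4.5, SD 3 | 51.9% | 5.0% | 5.0% | 5.2% |
| no effect, 4.5, SD 2.2 | 31.7% | 5.4% | 5.1% | 5.2% |

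Clipping shrinks the realised difference from 2 to between 1.67 and 1.94 points. That is why the t test sits a little under 80.8% in the SD 3 rows.

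**3. How far the switch rate depends on the assumptions.**

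- The no-effect range holds around a mean of 4.5. Nearer the floor it rises: 71% at mean 4 with SD 3, 80% at mean 3 with SD 2, and 100% at mean 2 with SD 3.
- If change from baseline is tested instead of the post-treatment score, Shapiro-Wilk fails in about 49-72% of simulated trials.
- A check by eye could pass more often than either.

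**4. What does the switch gain or lose?** In the table the t test holds its level. Its power exceeds Mann-Whitney's by at most 79.6 − 77.9 = 1.7 points, and the rule as written lies within 1.3 points of always using t (79.6 − 78.3). With more skewed beta-binomial scores, Mann-Whitney is sometimes ahead: 82.6% v 79.9% (means 5 v 3, SD 3) and 96.1% v 92.0% (means 4 v 2, SD 2.5). Even there, the t test keeps about the planned power or more.

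**5. Effect of the fix on power.** With pre-post correlation ρ, baseline adjustment reduces the SD to 3 × √(1 − ρ²). The values of ρ are assumptions.

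- ρ = 0.3: SD 2.86, power 84% at 37 per arm.
- ρ = 0.5: SD 2.60, power 90% at 37 per arm.

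**The case against.** The strongest reply is that this is a conventional rule that does no measurable inferential harm: power moves by a point or so and the type I error stays near 5%. That is correct, and it limits the point to what the primary test addresses. It does not remove the mismatch with the sample-size basis.

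Several stronger readings are tempting, and the document does not support them.

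- **A loss of power.** Applying the relative efficiency 0.955 gives 37 × 0.955 = 35.3 per arm and 78.9% power. That efficiency is for normal data, which the rule sends to the t test, so the figure describes a branch the plan does not take.
- **A switch that is nearly certain if TENS works.** This holds for means such as 4 v 2, which at SD 3 put about 31% of the active arm at 0. At 6 v 4 with SD 2.2 the switch rate is 39%. Pain on coughing or walking may lie further from the floor.
- **A result reported without an estimate or interval.** The section names tests and does not rule out estimates. Such reporting detail may sit in a document not shown, so its absence from an article is no finding.
- **Baseline adjustment lost through the switch.** The stated t test is unadjusted too. Adjustment is a benefit of the fix, not something the switch takes away.

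It can also be said that outcomes of different kinds may reasonably have different tests. That is true of pain against vital capacity. It is less persuasive for the same pain scale rated under different conditions.

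**Conclusion.** The point holds in a limited form. The article lets the observed distribution choose between a test of means and a rank test for the primary outcome, while 37 per arm was derived for a 2-point mean difference. This is a written rule, not a detail left for later.

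Under the assumed rounded and clipped normal scores and a Shapiro-Wilk check, the switch occurs in about 40-100% of trials with a 2-point underlying effect and in about 30-50% with none around a mean of 4.5. It is therefore plausible to likely, not certain. When it occurs, the primary test stops addressing the quantity the trial was sized on, and the pain conditions may not be comparable with one another.

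The cost lies in interpretation, not in error rates. The switch is not needed for validity. In the clipped-normal scenarios it brings no gain in power over always using t; under strong skew the gain is modest. The point should be corrected, but it does not threaten the trial.

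**What to change.** In Data analysis, drop the normality switch and name one primary estimator: the mean difference between arms in post-TENS NRS points with a 95% CI, adjusted for the pre-TENS score by ANCOVA, with robust standard errors if wanted. Use the same estimator for every pain condition. Report Mann-Whitney as a sensitivity analysis only, whatever the shape of the data.

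The pre-TENS score is already collected, so no new data are needed. The sample size stays at 37 per arm, and power rises above 80.8% to the extent that pre- and post-TENS scores correlate. The cost is a change of analysis wording, to be made before the data are unblinded.

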## Discussion

The use of TENS during the postoperative period has become more common in various types of surgery in recent decades [13,14,26,27]. The postoperative benefits of TENS exceed pain relief and include decreased analgesic consumption, deceased incidence of pulmonary complications (such as atelectasis) and improved pulmonary function [6,8,13,14,28]. Several authors have evaluated the postoperative effects of TENS following cardiac surgery and found that TENS reduces pain and the amount of analgesic consumption when compared to placebos or controls [8,27,29].

An improvement in respiratory muscle strength and increased pulmonary volumes and capacity, in addition to a reduction of pain after the use of low-intensity TENS was observed in the postoperative period of cardiac surgery. This study also showed that the group that underwent TENS experienced significant increases in both PImax and PEmax compared to the control group [6]. The effects of TENS on pulmonary function was also assessed in 31 patients undergoing coronary artery bypass grafting or valve replacement during the first 72 postoperative hours. Patients were randomly assigned to two groups: TENS and placebo. As a result, an improvement in the peak expiratory flow (PEF) values in the group that underwent TENS was observed; however, when both groups were compared, there were no significant differences in the forced vital capacity (FVC) and forced expiratory volume in 1 second (FEV1) values [29]. Similar results were observed in a study of 45 patients in which TENS was used as a postoperative complement to pharmacologic analgesia in patients undergoing coronary artery bypass grafting. The authors performed three spirometric measurements at 24, 48 and 72 hours after surgery and found that there were no significant improvements in the spirometric values of patients who were treated with TENS when compared with those receiving the placebo treatment [14].

The use of TENS increases the analgesic effect in patients undergoing a thoracotomy, providing an important analgesic strategy for the treatment of acute postoperative pain [24,25,28,30,31]. However, a study was conducted with 324 patients who underwent different types of chest surgery and concluded that TENS had little or no benefit after procedures associated with severe pain (posterolateral thoracotomy) [26]. Accordingly, the results after a lateral thoracotomy or sternotomy are varied; many studies advocate the efficacy of TENS in patients undergoing these surgeries, while others claim that TENS has little or no value after these procedures [26,32].

Here, we present the rationale and design for a randomized controlled trial comparing the effects of active TENS versus placebo TENS in patients undergoing nephrectomy. This is the first study to be conducted on the use of TENS in this population. The results of this study will be published when it is completed.

